## Study drug management

6

Two research drugs (eravacycline and tigecycline) have been approved for marketing by the National Medical Products Administration in China. The approved indications include complex abdominal infections in adults. Therefore, this study strictly followed the approved dosage for intravenous administration according to the instructions. The recommended dose of eravacycline is 1 mg/kg, which is administered every 12 h, and the duration of intravenous infusion is approximately 60 min. The recommended dosage for tigecycline is 100 mg for the first dose, followed by 50 mg every 12 h for intravenous infusion lasting 30–60 min. All the study treatments will last for 4–14 days. The total duration of treatment will be determined by clinical doctors based on the severity of the infection, patient clinical response, imaging studies, progress in bacteriology, and when possible, consultation with surgical and infectious disease experts. For patients with renal dysfunction or those who are undergoing hemodialysis, the dosage of the investigational drug does not need to be adjusted. The dose adjustment for patients with liver function impairment is shown in Table 1.

**Table 1 tab1:** Dose adjustment of the study drug.

	Eravacycline	Tigecycline
Normal hepatic function	1 mg/kg q12h	50 mg q12h (First dose 100 mg)
Child–Pugh A	1 mg/kg q12h	50 mg q12h (First dose 100 mg)
Child–Pugh B	1 mg/kg q12h	50 mg q12h (First dose 100 mg)
Child–Pugh C	On the first day, 1 mg/kg every 12 h Starting the next day, 1 mg/kg every 24 h	25 mg q12h (First dose 100 mg)
Renal insufficiency	No adjustment required	No adjustment required
Continuous renal replacement therapy	No adjustment required	No adjustment required

Resistance to tigecycline will be routinely tested as part of the study protocol. In cases where resistance is identified, the study will manage crossover treatments based on predefined criteria, and data on eravacycline resistance will also be collected and tested routinely to guide clinical decisions and ensure patient safety.

If a patient shows clinical improvement after ≥4 days of intravenous study treatment, the treatment can be stopped. If *Pseudomonas aeruginosa* is suspected or isolated, open-label amikacin or gentamicin can be added to any protocol based on the researcher’s judgment. Antifungal therapy is prohibited unless there is clear evidence of a pathogen. The research plan aims to minimize the likelihood of previous use of other antibiotics, which may confound the evaluation of treatment efficacy.

During the administration process, circulatory and respiratory functions will be continually monitored, and airway assistance measures, artificial ventilation, and other resuscitation devices will be readily accessible. Symptoms and fluctuations before and after administration will be recorded in the patients’ and nurses’ records. When adverse reactions occur, the symptoms, medication duration, dosage, and intervention measures will be recorded.

Eravacycline was acquired from Everest Medicine (Singapore) Pte Ltd., specification 50 mg, batch number AT3072B; tigecycline was obtained from CTTQ PHARMA, specification 50 mg, batch number 230504115.

The protocol will include a comprehensive screening process for known CYP3A4 inducers and inhibitors (Appendix). Patients with potent CYP3A4 inducers will be excluded from the study based on exclusion criteria. Patients on moderate or weak CYP3A4 inducers will be monitored closely, but no dosage adjustment will be made unless deemed necessary by the treating physician. In addition, patients on CYP3A4 inhibitors will be evaluated for potential drug–drug interactions, and appropriate measures will be taken to minimize the risk of adverse effects.

The protocol prohibits using medications that may interfere with the study drug’s efficacy or safety profile. This includes antibiotics with similar mechanisms of action or known to affect the study outcomes. A comprehensive list of prohibited medications is included in the study protocol’s Appendix, which will be provided to all participating sites and made available to investigators and participants upon request (Appendix).

## Population definition

7

The microbiologic modified intention to treat (mITT) population will include all patients with a confirmed diagnosis of complex abdominal infections (cIAIs) and positive infection source samples and/or blood sample cultures at baseline [excluding pathogens not expected to respond to either trial drug, such as nonfermenting gram-negative bacilli (e.g., *P. aeruginosa*, fungi, or mycobacteria)]. The mITT population will be used for demographic and baseline purposes.Clinical evaluation (CE) population: In the mITT population, researchers will follow the requirements of important components of the study protocol [such as cultivating baseline pathogenic gram-negative pathogens (reported in infection source samples and/or blood samples)], excluding those patients with pathogens (*P. aeruginosa*) who do not respond as expected to the investigational drug. This population will be used for clinical efficacy and all-cause mortality analysis.Microbiologically evaluable (ME) population: In the mITT population, individuals who have completed the study in accordance with important components of the study protocol and obtained baseline pathogenic gram-negative pathogens (reported in infection sources and/or blood samples) are expected to respond to the investigational drug. This population will be used for clinical efficacy, microbiological efficacy, comprehensive efficacy, and all-cause mortality analyses.Safety analysis (SS) population: Patients who have received at least one dose of the investigational drug during the clinical study period. The safety analysis population will be used for the analysis of safety data.

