## Abstract

**Background:**

Complicated intra-abdominal infections (cIAIs), often caused by multidrug-resistant bacteria such as carbapenem-resistant *A. baumannii* (CRAB) and carbapenem-resistant Enterobacteriaceae (CRE) are a critical challenge in ICUs. Owing to their high mortality and treatment failure rates, there is an urgent need for effective therapies. This trial will compare eravacycline to tigecycline for treating cIAIs in patients in the ICU, aiming to provide a superior treatment option.

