## Effectiveness evaluation

8

The primary efficacy end point is the all-cause 30-day mortality of patients in clinically evaluable and microbiologically evaluable populations.

The secondary efficacy endpoints are as follows: (1) the proportion of patients with a total response (composite endpoint consisting of clinical cure and microbiological response) in the clinically evaluable population at the end of treatment (days 5–14) and the test of cure visits (days 12 ± 2); (2) the proportion of total responsive patients in the microbiome-evaluable population at the end of treatment and the test of cure visits; (3) the proportion of microbiologically evaluable patients in the population with a total response to each pathogenic bacterium at the end of treatment and the test of cure visits; (4) the total response proportion of patients with drug-resistant bacterial infections in the microbiome-evaluable population at the end of treatment and the test of cure visits; (5) ICU hospitalization time and expenses; (6) quality of life outcomes or functioning after ICU discharge as assessed by application of the EuroQol-5D and Barthel Index scales; (7) changes in Sequential Organ Failure Assessment (SOFA) scores, reflecting the impact of the treatment on organ dysfunction over time; and (8) time to clinical improvement, measured from the start of treatment until the first observation of significant improvement in clinical status.

Given the variable susceptibility of MDR pathogens to tetracyclines, our study protocol will include analyses stratified by bacterial species. Specifically, subgroup analyses will be conducted for CRAB and CRE to gain a deeper understanding of the comparative efficacy of eravacycline versus tigecycline.

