## Data management and monitoring

10

All raw data (Table 3) will be meticulously recorded in the Case Report Form (CRF) by designated researchers. To ensure accuracy, each data entry will be independently double-checked by two individuals. The research coordinator at each center will supervise the data collection process, and the chief investigator, database administrator, and the statistician responsible for the statistical analysis will jointly determine the optimal database location strategy.

**Table 3 tab3:** List of data collection methods.

	Variables
Demographic data	Date of birth, sex, height, weight
Trial characteristics	Dates of screening and enrollment, inclusion criteria and consent details, date and time of randomization
Past medical history and risk factors	Past 3 months’ medical history, concomitant diseases, surgical history, allergic history, medication history (including immunosuppressive drugs, cytotoxic drugs, and biological agents), participation in other drug or medical device clinical trials
Infection and prognostic assessment	cIAI diagnosis time, presumed source of infection, invasive operation for source control, adequacy of source control, residue lesions, ICU admission time, APACHE II score, SOFA score
Antibiotic data	After the onset of the disease, all antibiotic usage, type/time/dose/route/frequency information
Clinical observations	Daily vital signs (blood pressure, heart rate, respiration, body temperature), clinical symptoms and signs, urine output, hematological variables, renal variables, hepatic variables, coagulation function, blood gas analysis, CRP, PCT, use of vasoactive drugs, catecholamine index, use of renal replacement therapy, mechanical ventilation duration, concomitant medication
Microbiological data	Date and time of initial peritoneal drainage culture, full susceptibility profile, daily peritoneal drainage culture results days 1 to 4; any further positive peritoneal drainage cultures and pathogen detection/resistance characteristics; other clinical sites growing *Escherichia*, *Klebsiella* or *Acinetobacter*, any multidrug-resistant organism, *P. aeruginosa* or *Clostridium difficile* identified within 30 days

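### The mITT exclusion names a class that takes in Acinetobacter, so sole-Acinetobacter patients leave the primary populations, against the planned CRAB subgroup and the trial's rationale

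*Protocol article*

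**What the plan says.** Section 7 (Population definition) builds mITT from patients with confirmed cIAI and a positive baseline culture, "excluding pathogens not expected to respond to either trial drug, such as nonfermenting gram-negative bacilli". A bracket then gives P. aeruginosa, fungi and mycobacteria as examples.

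Both evaluable populations are nested in that set: "Clinical evaluation (CE) population: In the mITT population" and "Microbiologically evaluable (ME) population: In the mITT population". Section 8 (Effectiveness evaluation) rests the main result on them: "The primary efficacy end point is the all-cause 30-day mortality of patients in clinically evaluable and microbiologically evaluable populations".

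The same section states that "subgroup analyses will be conducted for CRAB and CRE". It names no analysis population for those subgroups.

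Elsewhere A. baumannii is treated as a target:
- The Abstract calls these infections "often caused by multidrug-resistant bacteria such as carbapenem-resistant" A. baumannii and Enterobacteriaceae.
- The Introduction (section 1) cites in vitro activity of eravacycline against A. baumannii twice that of tigecycline.
- Table 3 (section 10) lists Acinetobacter among the organisms to be recorded.
- The Discussion (section 12) names P. aeruginosa as the one gap in eravacycline's spectrum. The CE definition likewise names only P. aeruginosa as not responding.

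**The concern.** A. baumannii is a nonfermenting gram-negative bacillus. The article does not say so, but this is basic microbiology. The mITT rule therefore classes one of the trial's motivating pathogens as unresponsive to both drugs, while the rationale says the opposite and a subgroup is planned for its carbapenem-resistant form.

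Two things are at stake. First, membership of the primary populations is unsettled for every patient with Acinetobacter alone: the wording puts them out, the evident intent puts them in. Secondly, the analyses meant to inform on CRAB lose their most direct evidence. These are the CRAB subgroup and, in ME, the response endpoints by pathogen and in drug-resistant infection. Loss of power is a lesser effect, of unknown size.

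**Working it through.** **Tracing the rule through the text**

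1. Section 7, mITT: the class of nonfermenting gram-negative bacilli is given as not expected to respond, and such pathogens do not qualify.
2. A. baumannii belongs to that class. No section exempts Acinetobacter.
3. The bracket does not narrow the class. Its species are introduced as examples, and fungi and mycobacteria are not gram-negative bacilli at all, so the bracket is garbled. If it were closed after P. aeruginosa, the whole class would still be excluded.
4. CE and ME are subsets of mITT, so whoever is outside mITT is outside both primary populations.
5. The rule removes pathogens, not patients. A patient with Acinetobacter and an eligible second organism can still enter mITT through the second organism. A patient with Acinetobacter alone cannot.
6. Exclusion criterion 4b (section 4.2) removes infections known to be resistant to a study drug. It works by susceptibility, not by species, so it does not settle the question.

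**The plan's own sample size**

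Inputs from section 11 (Statistics): control mortality p2 = 0.187; true ratio R1 = 0.95; noninferiority ratio R0 = 2; one-sided alpha 0.025; power 80%; 1:1 allocation. Hence p1 = 0.95 × 0.187 = 0.17765.

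Method: Farrington-Manning score test for a ratio of proportions.

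- Distance from the margin: d = R0·p2 − p1 = 0.374 − 0.17765 = 0.19635.
- Restricted estimates under p1 = 2·p2, with equal arms: 4q² − 3.55165q + 0.36465 = 0, so q2 = 0.1185 and q1 = 0.2370.
- Null variance term: V0 = q1(1 − q1) + 4·q2(1 − q2) = 0.5986.
- Alternative variance term: V1 = p1(1 − p1) + 4·p2(1 − p2) = 0.7542.
- Power = Φ[(d − 1.96·√(V0/n)) / √(V1/n)], with n patients per arm.

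At n = 131: (0.19635 − 1.96 × 0.0676) / 0.0759 = 0.842, and Φ(0.842) = 0.800. This reproduces 2 × 131 = 262. With dropout, 262 / 0.90 = 291.1, which gives 292 at 146 per arm. The sample size is sound on its inputs and is not at issue.

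**Illustration of the loss**

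The share of patients with Acinetobacter alone is not stated. Taking 5% and 20% of the 262 evaluable patients as assumptions (13 and 52 patients):

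| Share lost | n per arm | z | Power |
|---|---|---|---|
| 0% | 131 | 0.842 | 80.0% |
| 5% | 124 | 0.772 | 78.0% |
| 20% | 105 | 0.571 | 71.6% |

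The CRAB detection rates of 71.2% to 71.9% in the Introduction come from a national surveillance report. They are not the proportion of trial patients with Acinetobacter and cannot stand in for the missing share.

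**The case against.** The strongest defence is that the authors did not mean to exclude Acinetobacter. The operative test is whether a pathogen is expected to respond, the class name is only an illustration, and the rest of the article treats A. baumannii as in scope. That is probably a correct account of intent. It does not repair the text, because the sentence itself places the class among non-responders and nothing takes Acinetobacter back out.

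A reader might go further and infer that the CRAB subgroup would be empty and the trial unable to report on CRAB. The documents do not support this. The rule excludes pathogens, so polymicrobial cases can remain. Section 8 does not tie the subgroup to mITT, CE or ME, and section 4.3 describes an intention-to-treat analysis of all randomised patients, in which CRAB cases could still be examined.

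A reader might also infer bias from decisions made once cultures are known. The qualifying cultures are baseline samples and the data analysts are blinded (section 5). Clinicians do know the allocation, but nothing shows that the choice would differ by arm. The harm that can be shown is an unsettled population.

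The objection that the power range is speculative also stands. It depends on an assumed share and on those patients having no other eligible organism. The interim reassessment in section 11 could restore some power, but its stated trigger is divergent mortality, not a shrinking evaluable set.

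**Conclusion.** The mITT rule is wrong as written and contradicts the planned CRAB subgroup and the stated rationale. Patients whose only baseline pathogen is Acinetobacter fall out of mITT and so out of both primary populations. Within those populations, CRAB would be represented only by polymicrobial cases. This conclusion rests on the literal wording and on A. baumannii being a nonfermenter; it needs no numerical assumption.

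The effect on power cannot be determined from the article. A fall from 80% to about 78% to 72% illustrates an assumed loss of 5% to 20% and is not an estimate. The point deserves correction because it decides who enters the primary analysis, and the correction is cheap.

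**What to change.** In the mITT definition in section 7, replace the class name with the organisms already given as examples: P. aeruginosa, fungi and mycobacteria. State that Acinetobacter species count as eligible baseline pathogens in mITT, CE and ME.

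Leave CE's existing handling of patients with P. aeruginosa unchanged. CE excludes such patients without requiring P. aeruginosa to be the sole organism. A sole-pathogen condition carried into CE would admit mixed infections, in which section 6 permits added open-label aminoglycosides. That would be a substantive change to a primary population and is not needed here.

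Make the change as a dated amendment before any outcome data are compared by arm, including at the interim analysis planned at 50% of the data. The cost is one or two sentences of analysis-set wording; treatment, recruitment and the sample size calculation are unaffected.

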### Exit criteria

4.4

All patients who signed a written informed consent form and were screened as qualified to enter the study had the right to withdraw at any time. The exit criteria were as follows:

The patient or their authorized person refuses to continue the study or voluntarily withdraws informed consent;Patient death;Patients who are lost to follow-up;Poor compliance, no longer accepting the medication or testing before completing all studies, or inability to adhere to the study protocol to complete the study;Other situations that the researchers believe require withdrawal.

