Compared with tigecycline, eravacycline is a fully synthetic fluorocycline antibacterial drug. Eravacycline has been specifically modified on the D-ring: fluorine atoms are used to replace the C7 position, and pyrrolidone acetamide groups are used to replace the C9 position, achieving stronger antibacterial activity, improving drug permeability, increasing the tissue concentration, and increasing metabolic stability (20, 21). Eravacycline has a wide antibacterial spectrum and can cover common gram-positive, gram-negative, anaerobic bacteria and atypical pathogens, except for *P. aeruginosa*, especially MDRs that produce serine and metalloenzymes. Furthermore, eravacycline is either not affected or rarely affected by common tetracycline efflux pumps (tetA, tetB, tetK) and ribosomal protective protein (tetM) resistance genes (22). In most of the strains tested in *in vitro* experiments, the MIC of eravacycline was 2–4 times lower than that of tigecycline (9). Therefore, unlike tigecycline, physicians can reduce concerns about multidrug-resistant bacteria. In addition, in a phase I clinical trial of healthy subjects, the plasma and lung exposure levels of eravacycline were significantly greater than those of tigecycline (9.12 vs. 3.70 μg·h/ml and 9.18 vs. 6.32 μg·h/ml, respectively) (23, 24), suggesting the potential for enhanced clinical efficacy compared with that of tigecycline.

Owing to its lower apparent distribution volume (321 L vs. 639 L) and significantly shorter half-life than tigecycline (20 h vs. 42.4 h), eravacycline may reduce the adverse effects of drug accumulation. In their respective phase III clinical trials, digestive system adverse reactions were the most common, with an incidence rate of eravacycline<omadacycline<tigecycline (22). Other possible adverse reactions can be observed in the central nervous system; metabolic function; and the mental, urinary, and respiratory systems. Overall, the incidence rates of adverse reactions with eravacycline are lower than those with tigecycline and omadacycline (25). Recent meta-analyses have shown that, compared with that of tigecycline, the number of drug discontinuations due to adverse events is significantly lower (OR = 0.17, 95% CrI = 0.03–0.81) (26).

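### The ME population's pathogen rule refers to one undefined drug, so exclusions from the primary mortality analysis could differ by arm

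*Protocol article*

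**What the plan says.** The Effectiveness evaluation section (8) fixes the primary analysis: "The primary efficacy end point is the all-cause 30-day mortality of patients in clinically evaluable and microbiologically evaluable populations". Section 7 (Population definition) defines three nested efficacy populations with three different pathogen rules.

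- mITT, reserved for describing patients at baseline, is restricted by "excluding pathogens not expected to respond to either trial drug". *P. aeruginosa* is among its examples.
- CE, a subset of mITT, excludes patients with pathogens (*P. aeruginosa* in brackets) "who do not respond as expected to the investigational drug".
- ME, also a subset of mITT, requires baseline gram-negative pathogens that "are expected to respond to the investigational drug".

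The singular term is not defined. The antibiotic-related exclusion criteria (section 4.2, item b) bar infections known to be caused by a pathogen resistant to one of the two drugs, and use the plural. Section 4.3 provides for stopping treatment when a cultured strain proves resistant after dosing has begun. Section 6 says that resistance to both drugs is tested routinely and that crossover may follow.

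**The concern.** A filter on the primary analysis set must treat both arms alike. The mITT rule does so, because it names both drugs. The ME rule names one, and elsewhere the article uses that singular for the drug a patient is taking: in the withdrawal criteria of section 4.3, and in the safety population, defined as "Patients who have received at least one dose of the investigational drug during the clinical study period". Applied that way, a patient with a tigecycline-resistant, eravacycline-susceptible isolate leaves ME if assigned tigecycline and stays if assigned eravacycline. The reverse holds for an isolate resistant to eravacycline only.

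The article itself gives reason to expect isolates on which the drugs differ. The Introduction describes rising tigecycline resistance, and the Discussion reports eravacycline MICs 2–4 "times lower than that of tigecycline" in most strains tested. If patients with resistant isolates die more often, removing them from one arm changes that arm's mortality without any treatment effect.

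**Working it through.** **1. The plan's own figure.** Inputs from section 11: control mortality 18.7%, true ratio 0.95, noninferiority ratio 2, one-sided α 0.025, power 80%. The Farrington–Manning score test for a ratio of two proportions gives 131 per arm, so N = 262, at power 0.800. With 10% dropout, 262/0.9 = 291.1, which is 292 for two equal arms. The stated figures reproduce, so the point does not rest on the sample size.

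**2. Three readings of the ME rule.**

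- The drug received: the filter differs by arm.
- Eravacycline only: the filter is the same in both arms and the comparison stays randomised, but the population is selected on susceptibility to the test drug alone.
- Both drugs considered together: neutral, but not what the sentence says.

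Read naturally, the mITT step removes only pathogens that neither drug covers. An isolate covered by one drug passes mITT, and the ME wording decides whether it is kept. Exclusion item b catches such isolates only when the resistance is already known at entry.

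**3. Illustration, tigecycline arm filtered.** The shares are assumptions and none is in the document: *f* is the fraction of the arm removed and *m* the mortality among those removed. Mortality in those kept is (0.187 − f·m)/(1 − f). Eravacycline is held at 17.7%, which assumes no exclusions there. The unfiltered ratio is 0.177/0.187 = 0.95.

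| f | m | Tigecycline mortality kept | Ratio |
|---|---|---|---|
| 5% | 30% | 0.172/0.95 = 18.1% | 0.98 |
| 5% | 40% | 0.167/0.95 = 17.6% | 1.01 |
| 10% | 30% | 0.157/0.90 = 17.4% | 1.01 |
| 10% | 40% | 0.147/0.90 = 16.3% | 1.08 |
| 20% | 30% | 0.127/0.80 = 15.9% | 1.11 |
| 20% | 40% | 0.107/0.80 = 13.4% | 1.32 |

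The bias here runs against eravacycline. Every ratio stays below 2, so this scenario costs power and does not create a false noninferiority finding.

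**4. The opposite case, eravacycline arm filtered.** With true mortality 18.7% in both arms, the apparent ratio is [(0.187 − f·m)/(1 − f)]/0.187. It is 0.97 at f = 5%, m = 30%; 0.87 at 10%, 40%; and 0.58 at 20%, 50%. If the true ratio sits at the margin (eravacycline mortality 2 × 0.187 = 37.4%) and m is 50–60%, the score test with 131 tigecycline and 131(1 − f) eravacycline patients declares noninferiority with probability 0.03–0.04 at f = 5%, 0.04–0.05 at 10% and 0.06–0.11 at 20%, against a nominal 0.025.

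**5. The CE clause.** It names only *P. aeruginosa*. CE is drawn from mITT, and mITT has already removed *P. aeruginosa* in both arms. Taken with its bracketed example, the clause removes essentially nobody further.

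**The case against.** The strongest reply is that the singular is loose English. Section 6 uses it when saying that neither drug needs renal dose adjustment, and section 9 uses it for adverse events in both arms. Section 5 also keeps the data analysts unaware of treatment group, which fits poorly with a filter that depends on the assigned drug. This stands in part. A reader might infer that the plan certainly applies an arm-specific exclusion, and the document does not support that. It supports only that the sentence permits one and that no definition rules it out.

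Exclusion item b is a real mitigation. It acts before randomisation, ignores arm and targets the very isolates at issue. What remains is resistance first learned after randomisation, for which sections 4.3 and 6 explicitly plan.

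A reader might also infer from the CE wording that patients are removed for failing to respond. Read literally it does describe observed response. However, the only pathogen named is already gone at mITT, and beside the neighbouring definitions the phrase is probably poor wording for pathogens not expected to respond. It needs rewording but does not show outcome-based exclusion.

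The intention-to-treat statements in sections 4.3 and 11 give partial cover only, because section 8 places the primary endpoint in CE and ME.

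**Conclusion.** The point holds for ME: its pathogen rule is ambiguous, and one reading that matches the article's usage elsewhere would make exclusions from a primary analysis set differ by arm. For CE it is a lesser wording defect.

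Neither size nor direction can be fixed from the document. The ratios of 0.98 to 1.32 rest on assumed shares and on exclusions in the tigecycline arm only, and the figures for the eravacycline arm rest on the opposite assumption. A reader might infer from the lower eravacycline MICs that the bias has a known direction or favours eravacycline. The document does not support this: it gives no susceptibility criterion and no share of isolates resistant to either drug alone, and if tigecycline-only resistance did predominate, the bias would work against eravacycline. The wording should be corrected, because the ambiguity sits in the primary analysis and is cheap to remove.

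**What to change.** State one pathogen rule in section 7 and use it for both ME and CE. It should rest only on baseline isolates, be worded identically for both arms and match the mITT rule, so that a pathogen is excluded only if neither trial drug is expected to be active against it. Say that the decision is made without knowledge of assigned arm or outcome. In CE, replace the phrase about patients not responding as expected with wording about pathogens not expected to respond.

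This is a change of text plus a documented evaluability decision made blind. Isolates resistant to one drug then stay in both arms.

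The sponsor may prefer to require expected response to both drugs. That is also neutral between arms, but it departs from the mITT rule, leaves fewer drug-resistant cases for secondary endpoint 4 and shrinks the evaluable set. The plan allows for 10% loss. Under the planning assumptions, if 20% of the 146 per arm were not evaluable (116 left), power would be about 0.755, and at 30% (102 left) about 0.704.
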